**Figure 1 F1:**
[figure not shown]
Consolidated Standards of Reporting Trials (CONSORT) diagram of patient flow through the study.

### Intervention protocol

2.4

The interventions will be carried out twice a week for 2 months, for a total of 15 sessions, and will be performed by 2 experienced physiotherapists who are not evaluators, maintaining the blind nature of the method. For LLLT, the volunteers will be treated with low-level laser (Endolaser 476, Enraf Nonius, Rotterdam, The Netherlands), wavelength of 808 nm, 0.028 cm^2^ spot area, 100-mW power output, fluence of 200 J/cm^2^, energy per point of 5.6 J, in the regions of the lateral and medial epicondyle of tibia and femur, in the joint line of the lateral and medial knee, and the popliteal fossa (tendon of the biceps femoris, semitendinosus and between the tendons) and on the patellar tendon region, totaling 10 isolated points, for 56 seconds per point, total energy of 56 J. US will be applied using an aqueous gel as a coupling medium in circular movements with the probe at right angles. The treatment area is 25 cm^2^ and extends to both patellofemoral and tibiofemoral borders of the target knee on both the lateral and medial margins, avoiding the patella. Continuous ultrasonic waves with 1 MHZ frequency and 1 watt/cm^2^ power are applied with a 4-cm diameter applicator (Petson.250 ultrasound equipment Petas, Turkey) for 5 minutes in each session. To avoid the immediate effects of heat application, the outcome data evaluation is performed 2 days after completion of the last session.

### Primary outcome

2.5

The primary outcome is weekly change in pain intensity relative to baseline through 6 weeks of therapy, as measured on the VAS (0 = no pain, 10 = extreme pain). The VAS pain scale has been validated for consistency and reliability to assess pain associated with a variety of conditions, including osteoarthritis. Patients records their pain 4 hours after applying the device during daily treatment.

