### Random allocation

2.3

Before starting the study, a randomization list is produced using software-generated randomized numbers; the randomization depends on random blocks of 10 (Table 1). Patients will not know to which group they are assigned or which treatment they will be offered. Patients will be assigned at random to the ultrasound + LLLT group, LLLT group, or the ultrasound group. Participants are enrolled by the research assistant. After baseline examination, all patients will be given a full explanation of the treatment protocol and will be required to sign a written informed consent for study participation and for publication of the results. All the data collectors, surgeons, statistical analysts, as well as result assessors are not aware of grouping assignment (Fig. 1).

**Table 1 T1:** Patient baseline demographics.

Demographics	Combined group	LLLT group	Ultrasound group	*P* value
Number of patients (knees)				
Age at surgery^∗^ (years)				
Male sex (no. [%])				
BMI^∗^ (kg/m^2^)				
Right side (no. [%])				
Follow-up^∗^ (years)				

BMI = body mass index, LLLT = low-level laser therapy.

∗ The values are given as the mean and the SD.

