### Statistical analysis and power analysis

2.7

All analyses will be performed using SPSS for Windows, version 16, and GraphPad InStat. Analysis of variance is used for comparing mean values of patient's age, weight, height, and body mass index. For non-parametric measures like VAS and WOMAC, differences between baseline and post-treatment scores for each group are computed by the Wilcoxon signed ranks test. The difference between each treatment group is performed by the Kruskal–Wallis test. The level of statistical significance is set as *P* < .05. A power analysis is conducted to estimate the requisite sample size. From previous studies, a clinically significant difference reduction in the VAS was defined as 3 cm; a standard deviation of 3.49, probability of a Type I error of 0.05 and power of 0.8 resulted in an estimated sample size of 15. Consequently, a total of 120 subjects will be recruited.

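### The stated primary outcome (weekly VAS change through 6 weeks, under daily treatment) matches neither the twice-weekly schedule nor the single post-treatment analysis, and no one VAS value is named as primary

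*Protocol article*

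**What the plan says.** The protocol article describes the timing of VAS pain in several places.

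- **Section 2.5 (Primary outcome), repeated in the abstract:** "The primary outcome is weekly change in pain intensity relative to baseline through 6 weeks of therapy". Section 2.5 adds: "Patients records their pain 4 hours after applying the device during daily treatment".
- **Section 2.4 (Intervention protocol):** "The interventions will be carried out twice a week for 2 months, for a total of 15 sessions". It then fixes when outcomes are assessed, and why: "To avoid the immediate effects of heat application, the outcome data evaluation is performed 2 days after completion of the last session". VAS is not exempted.
- **Section 2.7 (Statistical analysis and power analysis):** for VAS and WOMAC, "differences between baseline and post-treatment scores for each group are computed by the Wilcoxon signed ranks test", followed by "The difference between each treatment group is performed by the Kruskal–Wallis test". Neither sentence names a week. The sample size rests on one VAS reduction of 3 cm, also undated.
- **Table 2 (in section 2.6):** one VAS row, beside WOMAC, ROM and muscle strength, which section 2.6 assesses at baseline and at the end of the study.

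**The concern.** Sections 2.5 and 2.4 describe different treatment frequencies. Section 2.5 describes a repeated weekly outcome, while section 2.7 and Table 2 describe a single before-and-after one. Nothing reconciles them, so a reader cannot tell which number is the trial's primary result.

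Two things are at stake. First, up to six weekly values and a post-course value all fit some part of the text. If none is named, the choice can be made after the results are known. Second, the candidates are different quantities: pain a few hours after a session part-way through treatment, or pain two days after the whole course. If staff follow section 2.5 alone and take no VAS at the two-day evaluation, that value cannot be recovered.

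A further question concerns heat. Section 2.4 delays the evaluation so that immediate heat effects have passed, whereas section 2.5 reads pain at 4 hours. The arms differ in heat exposure: "Patients will be assigned at random to the ultrasound + LLLT group, LLLT group, or the ultrasound group", and only the two arms with ultrasound receive it ("Continuous ultrasonic waves with 1 MHZ frequency"). Any heat effect still present at 4 hours would enter the comparison of combination with LLLT and largely cancel in the comparison of combination with ultrasound. This is conditional on an effect that the article does not quantify.

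**Working it through.** The article gives no figure to reproduce here. The check is a comparison of sections plus schedule arithmetic.

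**Inputs.** Two sessions a week and 15 sessions (section 2.4); evaluation 2 days after the last session (section 2.4); 6-week window and 4-hour reading (section 2.5). Assumptions: session 1 is on day 1, the first session of each week falls on the same weekday, and the second follows k days later, with k from 2 to 5.

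**Frequency**
- Twice weekly for 6 weeks: 2 × 6 = 12 sessions.
- Daily for 6 weeks: 5 × 6 = 30 sessions (five days a week) or 7 × 6 = 42 (seven days a week).
- The whole course is 15 sessions, so daily treatment for 6 weeks cannot be what section 2.4 describes.

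**Where week 6 falls in the course**
- Week 6 closes on day 6 × 7 = 42.
- Sessions given by then: 12/15 = 80%.
- Length of the course: 15/2 = 7.5 weeks.

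**Where the two-day evaluation falls**
- Session 15 is the first session of week 8: day 1 + 7 × 7 = 50.
- Evaluation: 50 + 2 = day 52.
- Gap from the close of week 6: 52 − 42 = 10 days.
- Session 12, the last in week 6, is on day 36 + k, that is day 38 to 41. The gap from its 4-hour reading to the evaluation is 52 − (36 + k) = 14 to 11 days.
- Time since the preceding application: 4 hours under section 2.5, 48 hours under section 2.4.

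**Endpoint against analysis**

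| Item | Section 2.5 and abstract | Sections 2.4, 2.7 and Table 2 |
|---|---|---|
| Treatment frequency | Daily | Twice a week |
| VAS values per patient after baseline | Weekly, up to six | One post-treatment score; one table row |
| Latest time | Week 6 | Two days after session 15 for outcome evaluation; undated in section 2.7 |
| Between-group test | None given | Kruskal–Wallis, no time point |

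**Illustration of an unnamed time point.** Suppose each of the six weekly changes were tested at 0.05 and any one success counted. With independent tests, the chance of at least one false positive is 1 − 0.95⁶ = 0.265. Weekly values in the same patient are correlated. A simulation of six three-group Kruskal–Wallis tests (40 per group assumed, 2,000 runs) gave about 0.22, 0.18, 0.13 and 0.13 at assumed correlations of 0.5, 0.7, 0.8 and 0.9. The article gives no correlation and does not say that every week will be tested, so this shows only why one value should be fixed.

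**The case against.** The best defence is that two VAS uses can coexist. Section 2.5 may describe a patient diary kept during therapy. The evaluation in section 2.4 may be the end-of-study assessment by evaluators, matching the timing that section 2.6 gives for WOMAC, ROM and strength. On that reading the 4-hour and two-day rules apply to different measurements and do not collide. This stands as a possible reading. The article refers to outcome data without limit, so it is not the only reading, but a contradiction on this point is not proven.

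It can also be said that an article condenses, and that the choice of week may be in a fuller document. That would answer a mere gap. It does not answer text that gives two treatment frequencies, or an analysis section that describes VAS in a form unlike the stated endpoint.

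A reader might infer four stronger things, which the article does not support:

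- *That heat biases the primary comparison.* Section 2.4 speaks of immediate effects, and nothing says whether any remain at 4 hours or how large they are.
- *That the 6-week window is itself an error.* A primary window may close before treatment ends. Stretching the 15 sessions over a full two months would widen the gap to the evaluation, but that departs from twice a week.
- *That the weekly outcome has no analysis at all.* Kruskal–Wallis could be run on any weekly change. The plan leaves this unspecified but does not exclude it.
- *That VAS will be missed at the two-day evaluation.* No section says so; it is only not assured.

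**Conclusion.** The point holds in this form. Daily treatment in section 2.5 contradicts twice-weekly treatment in section 2.4. The weekly endpoint does not match the single baseline versus post-treatment comparison in section 2.7 or the single VAS row in Table 2. No VAS value is identified as the primary result.

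The candidates are materially apart: 12 of 15 sessions at the close of week 6 against the full course, with about 10 days between that close and the two-day evaluation (11 to 14 days from the last 4-hour reading in week 6). These figures rest on a strict twice-weekly schedule from day 1 and the assumed 2 to 5 days between a week's sessions.

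The clash between the 4-hour reading and the two-day rule is conditional on that rule covering the patient-recorded VAS, and no bias size is claimed. Because the ambiguity concerns the primary result and is cheap to remove, it should be settled before unblinding.

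**What to change.** Before unblinding, name one primary VAS value and state that the planned Kruskal–Wallis test is applied to its change from baseline.

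- **Preferred:** the evaluation two days after session 15. This fits the protocol's own two-day rule and its post-treatment comparison. State that VAS is recorded at that visit, and keep the weekly values through week 6 as secondary.
- **If the sponsor prefers the 6-week endpoint:** name week 6 as primary, say which of that week's session readings counts, and state that the VAS diary is exempt from the two-day rule.
- **In either case:** replace the reference to daily treatment in section 2.5 with the twice-weekly sessions.

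Arms, treatment, sample size and planned test stay as they are. The cost is wording and at most one extra patient-recorded VAS at an evaluation already scheduled. The preferred option also changes the primary endpoint of a protocol that section 2.2 reports as approved and registered, so it needs a formal amendment, and its primary value is read about 10 days after week 6 closes. The second option avoids the change of endpoint but leaves the primary reading at 4 hours, where a heat effect cannot be ruled out from the article.

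### Sections 2.4, 2.5 and 2.7 disagree on when the primary pain score is taken, and the 2-day wait against heat effects cannot cover the weekly scores that Section 2.5 makes primary

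*Protocol article*

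**What the plan says.** Four places in the protocol article bear on the timing of the pain score.

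- **Section 2.5 (Primary outcome)** defines the endpoint: "The primary outcome is weekly change in pain intensity relative to baseline through 6 weeks of therapy, as measured on the VAS". It then fixes the moment of recording: "Patients records their pain 4 hours after applying the device during daily treatment".
- **Section 2.4 (Intervention protocol)** gives the schedule: "The interventions will be carried out twice a week for 2 months, for a total of 15 sessions". It describes the ultrasound as continuous ("Continuous ultrasonic waves with 1 MHZ frequency and 1 watt/cm^2^ power are applied with a 4-cm diameter applicator") and ends with a timing rule and its reason: "To avoid the immediate effects of heat application, the outcome data evaluation is performed 2 days after completion of the last session".
- **Section 2.3 (Random allocation)** names the arms: "Patients will be assigned at random to the ultrasound + LLLT group, LLLT group, or the ultrasound group". Ultrasound is therefore given in two of the three arms, and no sham ultrasound is described.
- **Section 2.7 (Statistical analysis)** says of VAS and WOMAC that "differences between baseline and post-treatment scores for each group are computed by the Wilcoxon signed ranks test", with Kruskal–Wallis for the comparison between groups. Table 2 has a single VAS row, under a title that calls the outcomes postoperative.

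**The concern.** The protocol names a measurement problem, sets a 2-day gap against it, and then defines its primary outcome by scores taken 4 hours after the device. The baseline examination precedes treatment. A weekly change built on 4-hour scores would therefore compare an untreated value with values from treatment days, and could mix lasting benefit with same-day relief.

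This matters for the comparison between arms because the heat sentence follows directly on the description of continuous ultrasound, which the LLLT arm does not receive. Any heat relief left at 4 hours could make the combined and ultrasound arms look better than LLLT alone without any lasting difference.

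The analysis text adds a second problem. It speaks of one post-treatment score, whereas Section 2.5 defines a weekly series. Two analysts could take different VAS values from the same patients and both claim to follow the protocol.

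**Working it through.** No figure in the document bears directly on this point, so there is none to reproduce. The check is a comparison of the texts, followed by an illustration on stated assumptions.

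**1. Can the 2-day wait apply to the weekly scores?** Inputs from Section 2.4: 2 sessions a week, 15 sessions. Input from Section 2.5: scores through week 6.

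- Sessions completed by week 6: 2 × 6 = 12 of 15.
- Time of the last session: 15 / 2 = 7.5 weeks.

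Every weekly score through week 6 is taken before the last session. None can be taken 2 days after it.

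**2. Is the 4-hour anchor workable?** Section 2.5 presupposes daily treatment and Section 2.4 two sessions a week. With two sessions a week, 7 − 2 = 5 days have no session from which to count 4 hours. If sessions were daily, 15 of them would end after 15 / 7 ≈ 2.1 weeks, which fits neither 2 months of treatment nor 6 weeks of therapy. The text does not say how a weekly value is formed.

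**3. Which score is tested?**

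| Place | VAS value implied |
|---|---|
| Section 2.4 | one evaluation, 2 days after the last session |
| Section 2.5 | weekly values through week 6, each 4 hours after the device |
| Section 2.7 | baseline against a post-treatment score |
| Table 2 | one VAS row per group |

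Sections 2.4 and 2.7 and Table 2 can be read together as a single end-of-treatment score. Section 2.5, which carries the primary definition, cannot be read that way.

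**4. Which contrasts would be affected?** Let *h* be heat relief remaining at 4 hours, assumed equal in both ultrasound-containing arms and zero under LLLT alone. With no lasting difference between arms:

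- combined minus LLLT = *h*
- ultrasound minus LLLT = *h*
- combined minus ultrasound = *h* − *h* = 0

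**5. Illustration of size.** From the document: SD 3.49 and the 0.05 level. Assumed: 40 per arm (120 / 3; the allocation ratio is not stated), normally distributed changes, SD 3.49 applied to those changes, and the values of *h*.

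A pairwise normal approximation, two-sided 0.05, has SE = 3.49 × √(2/40) = 0.780 and rejection probability ≈ Φ(*h*/SE − 1.96). A simulation of 20,000 trials applied Kruskal–Wallis to all three arms.

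| Assumed *h* (cm) | *h*/SE | Pairwise, ultrasound-containing arm vs LLLT | Kruskal–Wallis, three arms |
|---|---|---|---|
| 0 | 0 | 5% (nominal) | 4.8% |
| 0.5 | 0.641 | Φ(−1.319) ≈ 9% | 9.1% |
| 1.0 | 1.281 | Φ(−0.679) ≈ 25% | 22.7% |
| 1.5 | 1.922 | Φ(−0.038) ≈ 48% | 46.0% |

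A repeat of the simulation gave 4.8%, 9.3%, 22.6% and 46.5%. With an assumed SD of 2.5, the rates for the three non-zero shifts were 12.8%, 40.9% and 77.0%. All these rates follow from the chosen shifts and say nothing about how likely those shifts are.

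**The case against.** **The tested score may already be protected.** Section 2.7 and Table 2 fit one VAS taken 2 days after the last session, with the 4-hour entries serving only as an on-treatment diary. This reading is open and the text does not exclude it. It conflicts, however, with the primary outcome as defined in Section 2.5. The objection turns the point from an established bias into an unresolved definition, but it does not remove the need to amend.

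**Nothing shows that heat relief lasts 4 hours.** A reader might infer that transient relief does enter the primary outcome, and unequally by arm. The document does not support this. It speaks of immediate effects without giving their duration or size, and does not say that 2 days is the minimum needed. For the same reason, 4 hours being one twelfth of 48 hours measures no bias. What stands is a risk on the protocol's own reasoning: having chosen 2 days, it gives no reason to treat 4 hours as safe.

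**The imbalance is inferred.** It rests on the heat sentence following the ultrasound description. The Introduction credits both modalities with analgesia associated with muscle relaxation and better microcirculation, so LLLT may give same-day relief too, and the effects need not add up. The claim of synergy also needs the combination to beat ultrasound alone, where shared heat relief would largely cancel. This objection stands as a limit on the consequence.

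**Pain during therapy is a legitimate target.** If that is what the sponsor wants, a difference at 4 hours is real for that target and not a false positive. The objection holds in principle, but the rationale in Section 2.4 points the other way. The sponsor has to say which is meant.

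**Conclusion.** The conflict on timing is established from the text alone. The 2-day safeguard cannot cover weekly scores taken through week 6 of a course that runs to about 7.5 weeks. The word *daily* contradicts twice a week, and it is unclear which VAS is tested.

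The consequence is conditional. If the 4-hour score is tested, and if heat relief remains at 4 hours, the result could favour the two ultrasound-containing arms over LLLT alone, with little effect on combined versus ultrasound. The rates of about 9%, 23% and 46% are illustrative only. They rest on assumed shifts of 0.5, 1.0 and 1.5 cm, equal in both ultrasound-containing arms and absent under LLLT alone, with 40 per arm and no lasting difference. Actual contamination of the primary outcome is not shown. Settle the point before scores are collected, because a score taken at the wrong time cannot be recovered afterwards.

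**What to change.** 1. Reconcile Sections 2.4, 2.5 and 2.7 and Table 2, including the daily and twice-weekly descriptions of treatment, and state which VAS score is primary and which is entered in the test.
2. In line with the reason given in Section 2.4, replace the 4-hour sentence in Section 2.5. Record the weekly primary VAS just before the week's first session, at least 2 days after the previous session, in the same way in all three arms. On the schedule in Section 2.4, the week-6 value would be taken before session 13.
3. If the 4-hour score is kept, label it a secondary measure of same-day response.
4. If the sponsor instead wants on-treatment pain as the primary target, say so and explain why the concern about heat in Section 2.4 does not apply to it.

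The cost is a short amendment and a change to the pain diary. On a twice-weekly schedule patients already attend, so no visit is added, and the change alters assessment timing only, not treatment. The downside is that same-day relief no longer counts in the primary outcome, so the reported improvement may be smaller.

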### Secondary outcomes

2.6

Secondary outcome measures assessed are change in WOMAC score for pain stiffness and function, ROM, and muscle strength assessed at baseline and the end of the study. ROM and strength measurements are acquired by trained clinic staff on a small pilot cohort of sequentially enrolled patients using computerized dual inclinometry ROM and muscle tester equipment (JTECH Medical, Midvale, UT). To assess ROM, 1 inclinometer is positioned on the quadricep muscle at mid femur and the other at mid-tibia. Patients are asked to lay flat on their back and lift their leg and flex at the knee to measure flexion. Patients are then asked to sit at the edge of the table and extend their leg to measure extension. To assess muscle strength, a manual muscle tester is used. Patients are asked to sit at the edge of the table with their knee at approximately 90 degrees. The manual muscle tester is positioned and hold at anterior mid tibia while patients are asked to extend their leg to measure extension strength. To measure flexion strength, the muscle tester is held at anterior mid-tibia and the patient is asked to flex at the knee. Each ROM and muscle strength test is repeated 3 times and the average is recorded (Table 2).

**Table 2 T2:** Postoperative outcomes.

Outcomes	Combined group	LLLT group	Ultrasound group	*P* value
VAS				
WOMAC				
ROM				
Muscle strength				

LLLT = low-level laser therapy, ROM = range of motion, VAS = visual analog scale, WOMAC = Western Ontario and McMaster Universities Osteoarthritis Index.

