To our knowledge, only Paolillo et al tried to evaluate the synergistic effects of ultrasound and LLLT in patients with knee osteoarthritis. However, the sample size of their study was too small to draw convincing conclusions, thus further research is needed to confirm the synergies.^[13]^ Therefore, we will conduct this present randomized double-blind study to evaluate the synergistic effects of simultaneously applying ultrasound plus LLLT on pain and muscle function in patients with knee osteoarthritis. It is assumed that there will be a remarkable difference in postoperative outcomes between the intervention and control groups.

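### Flexion strength is to be tested with the device on the front of the shin, where it cannot resist flexion, and section 2.6 contradicts itself on which patients have ROM and strength measured

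*Protocol article*

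**What the plan says.** The Introduction gives the aim as "to evaluate the synergistic effects of simultaneously applying ultrasound plus LLLT on pain and muscle function in patients with knee osteoarthritis". The Abstract and the Discussion repeat it.

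Section 2.6 (Secondary outcomes) opens with a list that carries no restriction: "Secondary outcome measures assessed are change in WOMAC score for pain stiffness and function, ROM, and muscle strength assessed at baseline", and again at the end of the study. Table 2, in the same section, has rows for VAS, WOMAC, ROM and muscle strength, with a column for each of the three groups and one for a P value.

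The second sentence of section 2.6 narrows this: "ROM and strength measurements are acquired by trained clinic staff on a small pilot cohort of sequentially enrolled patients". The article does not give the cohort's size or its split by arm.

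On the strength test, the patient sits at the edge of the table with the knee at roughly 90 degrees. For extension: "The manual muscle tester is positioned and hold at anterior mid tibia while patients are asked to extend their leg". For flexion: "To measure flexion strength, the muscle tester is held at anterior mid-tibia and the patient is asked to flex at the knee". Each ROM and strength test is done three times and averaged.

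Section 2.7 sizes the trial on VAS alone: "Consequently, a total of 120 subjects will be recruited". Section 2.3 names three arms: "Patients will be assigned at random to the ultrasound + LLLT group, LLLT group, or the ultrasound group".

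**The concern.** There are two separate faults, both in section 2.6.

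The first is the measurement itself. A hand-held tester records the force pressed against it, so it must lie on the side towards which the limb moves. The text gives the same site for two opposite movements. Staff who follow it would record flexion-strength values that do not measure flexion strength. More patients would not repair this, and the data could not be recovered afterwards.

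The second is who is measured. Muscle function is one of the two targets named in the objective, and strength is the only direct muscle measurement in the article. One sentence makes it an outcome of the whole trial and the next confines it to a small subset. A reader of the completed Table 2 could take the strength and ROM rows to rest on the same patients as the VAS row when they may rest on far fewer. The article justifies the trial by saying that the earlier study of this combination was too small to convince. A small subset would leave the strength comparison with the same weakness.

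**Working it through.** The plan gives no sample size, effect or power for strength or ROM, so there is no figure to reproduce. Both parts rest on reading the text. The arithmetic only shows scale.

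**Tester position**

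| Test | Start position | Movement of the shin | Stated site | Does the site oppose the movement? |
|---|---|---|---|---|
| Extension | Seated, knee about 90 degrees | Forward | Front of mid-tibia | Yes |
| Flexion | Seated, knee about 90 degrees | Backward | Front of mid-tibia | No |

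No strap or tether is described that would let a device on the front resist a backward movement. In flexion the shin leaves the pad, which would register little or nothing.

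**Who is measured**

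| Place | What it implies for ROM and strength |
|---|---|
| Abstract, Introduction, Discussion (objective) | Muscle function is a target of the trial |
| Section 2.6, first sentence | Secondary outcomes at baseline and end of study, no restriction |
| Section 2.6, second sentence | Acquired in a small pilot cohort |
| Section 2.6, Table 2 | Compared across three groups with a P value, beside VAS and WOMAC |

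The second sentence of section 2.6 does not fit with the other three places.

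**Scale if the subset stands (illustration)**

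Inputs:
- Total of 120 (section 2.7) in three arms (section 2.3). The allocation ratio is not stated. Assuming 1:1:1, 120 / 3 = 40 per arm.
- Pilot cohort: no size is given. Assumed 30 (10 per arm) or 60 (20 per arm).
- Two-sided alpha 0.05 and power 0.80. Section 2.7 uses 0.05 and 0.8 for VAS; two-sided is an assumption.

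Normal approximation for the smallest detectable difference between two arms, in SD units: (1.960 + 0.842) × √(2/n). The exact two-sample t calculation is alongside.

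| n per arm | Normal approximation | Two-sample t |
|---|---|---|
| 10 (assumed) | 2.802 × √0.2 = 1.25 | 1.32 |
| 20 (assumed) | 2.802 × √0.1 = 0.89 | 0.91 |
| 40 (all 120) | 2.802 × √0.05 = 0.63 | 0.63 |

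For an assumed true difference of 0.5 SD, power (normal approximation) is 20% at 10 per arm, 35% at 20 and 61% at 40.

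**Workload if everyone is measured**

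Four tests (ROM flexion, ROM extension, strength extension, strength flexion) × 3 repeats × 2 visits = 24 readings per patient. For 120 patients, 24 × 120 = 2,880 readings.

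**The case against.** The strongest reply concerns scope. Pain is the sole primary outcome and the trial is sized on VAS, while strength and ROM are secondary. Measuring a secondary outcome in a subset can be legitimate. A run of consecutively enrolled randomised patients still gives a randomised comparison. WOMAC function is not confined to the pilot cohort, so patient-reported function would be assessed in everyone. All of this stands, and it limits the point to the secondary outcomes. It does not remove it, because WOMAC is a questionnaire score and does not measure muscle strength.

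A reader might infer that half of the trial's question will be answered from a handful of patients. The document does not support that. It contradicts itself on who is measured, and if the restriction is a drafting error there is no loss of power. Being one of two named targets also gives muscle function no fixed weight.

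A condensed article may leave the subset's size and selection to the full protocol, so their absence is not counted here. Condensing does not explain an explicit restriction that clashes with the sentence before it, nor a stated device site that cannot work.

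The detectable differences rest on assumed sizes and a pairwise t-test, whereas the between-group test named in section 2.7 is Kruskal–Wallis. They do not describe the planned analysis.

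On the tester, a reader might infer that an anterior pad would record extension force during the flexion test, or that all the strength data are spoiled. Neither follows. The pad would record little or nothing in flexion, and the extension test is coherent as written. The flexion sentence may simply repeat the site from the extension sentence, but staff would still be following the wrong text.

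**Conclusion.** The point holds in two limited parts.

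First, the flexion-strength procedure is wrong as written. This rests on the seated position at about 90 degrees and on there being no strap or tether, as described. The fault is confined to one direction of one secondary outcome.

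Second, the text is inconsistent on whether ROM and strength are measured in all randomised patients or only in a pilot cohort. The contradiction is certain; its consequence is conditional. Only if the subset governs does precision fall, from about 0.63 SD detectable with all 120 to roughly 0.9 to 1.3 SD at the assumed 20 to 10 per arm. In that case the strength results could not support a trial-level conclusion on muscle strength.

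The primary pain comparison is unaffected by either part. Both should be corrected before measurements are taken.

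**What to change.** 1. **Flexion strength.** Change the tester position for the flexion test to the posterior side of the shin, so that the device resists the movement, and leave the extension position as it is. This is an edit of one word or so and needs no new equipment.

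2. **Who is measured.** Reconcile the two opening sentences of section 2.6 with Table 2 and the objective, by one of two routes:
   - *The subset is intended.* Give ROM and strength their own n in Table 2, label them exploratory, and draw no trial-level conclusion on muscle strength. The objective in the Abstract, Introduction and Discussion should be qualified to match. The cost is editorial, but it touches the stated aim of a registered study.
   - *The restriction is a drafting error.* Delete it, so that all randomised patients are measured at baseline and end of study. The cost is real: 24 readings per patient, 2,880 in all if 120 are measured, which may need staff time beyond what is available now.
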